## Abstract

**Background and Aims:**

Digital interventions are effective for reducing alcohol consumption but evidence is limited regarding smartphone apps. Drink Less is a theory‐ and evidence‐informed app to help people reduce their alcohol consumption that has been refined in terms of its content and design for usability across the sociodemographic spectrum. We aim to evaluate the effectiveness and cost‐effectiveness of recommending Drink Less at reducing alcohol consumption compared with usual digital care.

**Design:**

Two‐arm individually randomised controlled trial.

**Setting:**

Online trial in the United Kingdom (UK).

**Participants:**

Hazardous or harmful drinkers (Alcohol Use Disorders Identification Test [AUDIT] score ≥8) aged 18+ who want to drink less alcohol (*n* = 5562). Participants will be recruited from July 2020 to May 2022 using multiple strategies with a focus on remote digital methods.

**Intervention and comparator:**

Participants will be randomised to receive either an email recommending that they use Drink Less (intervention) or view the National Health Service (NHS) webpage on alcohol advice (comparator).

**Measurements:**

The primary outcome is change in self‐reported weekly alcohol consumption, assessed using the extended AUDIT‐Consumption, between baseline and 6‐month follow‐up. Secondary outcomes include change in self‐reported weekly alcohol consumption assessed at 1‐ and 3‐month follow‐ups, and the proportion of hazardous drinkers; alcohol‐related problems and injury; health‐related quality of life; and use of health services assessed at 6‐month follow‐up. Effectiveness will be examined with adjusted regression models, adjusting for baseline alcohol consumption and using an intention‐to‐treat approach. A mixed‐methods process evaluation will assess engagement, acceptability and mechanism of action. Economic evaluations will be conducted using both a short‐ and longer‐term time horizon.

**Comments:**

This study will establish the effectiveness and cost‐effectiveness of the Drink Less app at reducing alcohol consumption among hazardous and harmful adult drinkers and will be the first randomised controlled trial of an alcohol reduction app for the general population in the United Kingdom. This study will inform the decision on whether it is worth investing resources in large‐scale implementation.

## INTRODUCTION

Hazardous and harmful alcohol consumption is a major public health concern and contributes to health inequalities with the most deprived groups suffering the most harm from alcohol [1]. Fewer than 7% of hazardous and harmful drinkers receive face‐to‐face interventions in primary care to support alcohol reduction [2] with key barriers to the delivery of these interventions by practitioners being lack of time and low confidence about discussing alcohol with patients [3, 4]. Digital interventions, such as websites and smartphone apps, may be effective for reducing alcohol consumption [5] and may overcome barriers to delivery of face‐to‐face interventions because they potentially have a broad reach and relatively low implementation costs (once developed) and therefore can be delivered at scale [6]. As digital technologies become more integrated into everyday life and widely used, digital interventions can have a large positive impact on public health and well‐being at a population level. Smartphone apps are a promising mode of intervention delivery because smartphones have become increasingly affordable to end users and prevalent among the United Kingdom (UK) population [7]. However, most digital alcohol interventions that have been evaluated are web‐based and there is little evidence on the effectiveness of apps. The few trials of apps have been based in other countries and usually with younger adults [8, 9, 10, 11]. Therefore, there is an urgent need for a robust evaluation of an evidence‐ and theory‐informed alcohol reduction app, which, if effective, could be widely recommended to drinkers in the UK. The Drink Less app was designed to help people reduce their alcohol consumption and has been developed and refined using a systematic and iterative process [12, 13]. The app is ready for a definitive evaluation to establish whether recommending it to people is more effective than usual digital care for the reduction of alcohol consumption.

Digital interventions—primarily web‐based—may reduce alcohol consumption, with an average reduction of 23g of alcohol (2.9 UK units) per week compared with participants in the control group [5]. In this Cochrane review of 42 randomised controlled trials (RCTs), only one of the digital interventions used a smartphone app, and this RCT was conducted in Sweden among university students, which found that the app may have led to a negative effect among men [8]. Updates of this review found a further three studies that used smartphone apps: one in Sweden among university students (that found the app had potential for reducing excessive alcohol use) [9], one for the general population in Canada (that found that access to the app had no impact on drinking) [10] and another for young adults in Australia (that found a decrease in the typical number of drinks on a drinking occasion in both conditions) [11]. Therefore, despite the availability of hundreds of alcohol‐related apps, none have been evaluated in a RCT among the general population of adults in the United Kingdom. The majority have also been developed without reference to scientific evidence or theory [14]. The lack of evidence highlights the necessity of a robust and pragmatic evaluation of an evidence‐ and theory‐informed alcohol reduction app, which, if effective, could be widely recommended.

Drink Less is an evidence‐ and theory‐informed app that aims to help hazardous and harmful drinkers reduce their alcohol consumption. Drink Less is one of the most popular alcohol reduction apps on the UK Apple app store and is highly rated by users, and is capable of reaching a large proportion of the UK population at a low incremental cost. The development and evaluation of Drink Less was guided by the Medical Research Council's guidance on complex interventions [15] and the Multiphase Optimisation Strategy [16]. The development of the Drink Less app was informed by the COM‐B model of behaviour [17] and multiple sources of evidence [14, 18, 19] meaning it has a robust theoretical basis and evidence base. The COM‐B model posits that behaviour results from interactions between ‘capability’, ‘opportunity’, and ‘motivation’, and was used to provide an overarching theoretical structure [17]. The empirical evidence and theoretical framework provided the basis for the prioritisation of intervention components to include in the app. Drink Less consists of seven key modules: (i) Goal Setting; (ii) Self‐Monitoring and Feedback; (iii) Normative Feedback; (iv) Cognitive Bias Retraining; (v) Action Planning; (vi) Behavioural Substitution; and (vii) Information About Antecedents. Details of these modules are reported in full elsewhere [12]. A factorial screening trial was conducted to identify the most effective modules (distinct behaviour change interventions) within the app, which established that four of the five original modules appeared to have an effect on reducing alcohol consumption after 4 weeks if combined with one of the other modules [13]. Data also suggested that users of Drink Less found it to be engaging [13], which is important to reduce participant attrition. The strategy for refining the effectiveness and usability of the app was based on: (i) findings from the previous factorial trial; (ii) a content analysis of user feedback (that indicated that users found it helpful in reducing their drinking); and (iii) an updated evidence review and meta‐analysis of behaviour change techniques in digital alcohol interventions. The refinement process is reported in full elsewhere (under review). Both the initial development and refinement of Drink Less have involved input from users across the social spectrum on the functionality, design and language used in the app [20]. The same approach was used for a smoking cessation digital intervention that was found to be effective for increasing smoking cessation rates across different socioeconomic groups [21].

The next step in the Multiphase Optimisation Strategy is to conduct a RCT to evaluate the long‐term effectiveness and cost‐effectiveness of the digital recommendation of the refined Drink Less app, compared with alcohol advice from the National Health Service (NHS) alcohol advice webpage (usual digital care, available to anyone seeking alcohol support), in reducing alcohol consumption among hazardous and harmful drinkers. This research will be the first RCT of an alcohol reduction app for the general population in the United Kingdom and will evaluate whether it is worth investing resources into promoting and disseminating the app on a larger scale. The aim of this trial is to evaluate the effectiveness and cost‐effectiveness of recommending Drink Less at reducing alcohol consumption compared with usual digital care.

### Research questions

Among hazardous and harmful drinkers, does the digital recommendation to use Drink Less compared with the NHS alcohol advice webpage reduce weekly alcohol consumption (in UK standard units) between baseline and 6‐month follow‐up?Among hazardous and harmful drinkers, does the digital recommendation to use Drink Less compared with the NHS alcohol advice webpage:Reduce weekly alcohol consumption (in UK standard units) between baseline and 1‐ and 3‐month follow‐up?Reduce heavy episodic alcohol consumption at 6‐month follow‐up?Reduce the proportion of hazardous drinkers at 6‐month follow‐up?Reduce alcohol‐related problems and injury, and use of healthcare services at 6‐month follow‐up?Improve health‐related quality of life at 6‐month follow‐up?What is the extent of user engagement with Drink Less and does user engagement moderate these outcomes?Through what psychological measures does engagement with Drink Less change drinking behaviour?What are participants' views on the acceptability of the intervention?What is the cost‐utility and potential impact on health inequalities of Drink Less compared with the NHS alcohol advice webpage in terms of reduction in alcohol consumption and health‐related quality of life using a short time horizon?What is the longer‐term cost‐effectiveness and potential impact on health inequalities of Drink Less compared with the NHS alcohol advice webpage, if rolled out on a national level through active promotion to the public, over a 20‐year period?

## METHODS

### Design

A two‐arm, parallel group, RCT with a 1:1 allocation comparing the recommendation to use the intervention (Drink Less) with usual digital care (the NHS alcohol advice webpage), with an embedded mixed‐methods process evaluation.

### Setting

The study will take place online with participants who live in the UK.

### Participants

Participants will be included if they: are aged 18 years or over, live in the UK, are hazardous and harmful drinkers (Alcohol Use Disorders Identification Test (AUDIT) score ≥8), have access to an iOS device (i.e. iPhone, iPod touch or iPad, because Drink Less is currently only available on these devices) and want to drink less alcohol. Participants will be excluded if they are unwilling to complete follow‐up assessments or are unable to read English (for pragmatic reasons), which will be assessed with a Yes/No question in the screening questionnaire.

### Recruitment

Recruitment is due to run from July 2020 to March 2022 via a multi‐pronged strategy including: an advertisement on the NHS website; a mail‐out to a database of UK‐based users of the Smoke Free app; and press releases and local advertising through health care providers and/or national and local government colleagues. The advertisements will be co‐developed with public representatives.

### Sample size

A sample size of 5562 participants (2781 in the comparator group and 2781 in the intervention group) is required to detect a mean difference reduction of 2 UK units (16 g of alcohol) in weekly alcohol consumption (the primary analysis) at 90% power with an α of 0.05 and a two‐tailed test. This was calculated using G*Power software [22]. The estimated effect size is in line with the Cochrane review on digital alcohol interventions [5] and is roughly equivalent to that found in face‐to‐face brief interventions [23].

An initial sub‐sample of 26 participants (13 from each group [24]), who consented to a short interview about their experience of the trial, will be selected after the 6‐month follow‐up, as part of the mixed‐methods process evaluation. Participants will be purposively sampled to achieve good diversity in terms of sociodemographic characteristics and with high and low engagement. Data will be analysed and data collection will continue only if thematic ‘meaning’ saturation is not reached (see Analysis). Collection will continue in an iterative process (adding 10 participants at a time) until saturation is reached.

### Intervention

Drink Less is a stand‐alone app‐based intervention that is freely available via the Apple app store in the UK [25]. Drink Less was developed for hazardous and harmful drinkers to help them reduce their alcohol consumption. Drink Less consists of evidence‐based modules to help users change their drinking behaviour: Goal Setting, setting weekly ‘drinking reduction’ goals; Self‐Monitoring and Feedback, monitoring alcohol consumptions and seeing progress on goals; Action Planning, creating plans for dealing with difficult drinking situations; Normative Feedback, providing personalised feedback on how an individual's drinking behaviour compares to the norm; Cognitive Bias Re‐Training, a game for retraining users' automatic biases for alcoholic drinks; Behavioural Substitution, planning to substitute drinking with a neutral behaviour; and Information about Antecedents, providing users with information about situations and events, emotions and cognitions that predict their drinking. These evidence‐based modules map to behaviour change techniques (Fig. 1). The development and content of the original Drink Less version is reported in full elsewhere [12] and the refined version is reported online (https://osf.io/mc8yz/). The app contains standard features such as the UK Chief Medical Officers' low‐risk drinking guidelines (14 units a week) [26].

**Figure 1 add15287-fig-0001:**
[figure not shown]
Logic model for the process of change of the Drink Less app (developed by the internal research team). [Colour figure can be viewed at wileyonlinelibrary.com]

On downloading the app, users are asked to complete the AUDIT, provide sociodemographic details and then receive the Normative Feedback module. Users are then guided through setting a goal and shown how to use the key features of the app. Users can access all of the modules from the dashboard and the menu bar. The dashboard (the landing page of the app) has suggestions for the user to complete each day, as well as features of and links to the modules. Users can choose to have daily reminders to complete their drinks and mood diary for the previous day. The app provides a ‘toolbox’ of features for users to choose from and access as and when they want. The app is not tailored to the user except for personalised feedback in two modules: Normative Feedback and Self‐Monitoring and Feedback. Any modifications to the app during the trial (e.g. bug fixes) will be documented and reported.

Drink Less is expected to reduce the alcohol consumption of its users based on (i) its robust theoretical basis (the COM‐B model of behaviour) [17]; (ii) its evidence base; and (iii) user feedback that indicates users believe that it helps them to reduce their drinking and has a positive effect on their health and well‐being. It is also expected to reduce urges to drink, increase motivation to drink less and increase self‐regulatory capacity to drink less (see Fig. 1 for the logic model). Drink Less is also highly rated by users (average 4.2‐star rating in the Apple (UK) App Store with over 60 000 unique users as of 1 November 2019).

### Comparator

The comparator group will receive the recommendation to view the NHS alcohol advice webpage on ‘Tips on cutting down’ that also has links to other webpages aimed at hazardous and harmful drinkers [27]. This can be considered reflective of ‘usual digital care’ in this context because it is the digital support currently available to treatment‐seeking individuals from the NHS. Therefore, this comparator best serves the primary purpose of the trial [28], which is to investigate whether it is worth promoting Drink Less over the ‘usual digital care’ and is of direct policy relevance. Furthermore, it is important to have a comparator that is relevant to the same target population as the intervention, and both Drink Less and the NHS webpage are aimed at adults in the general population. Any changes to the comparator during the trial will be documented.

This is a pragmatic trial where participants have access to a wide range of digital support and therefore it is not possible to simply compare use of the Drink Less app with use of the NHS webpage to assess which is more effective. Instead, the pragmatic nature of the trial means the evaluation is in terms of whether the recommendation of the Drink Less app enhances usual digital care over and above what is currently used by the participant.

### Procedure

Figure 2 illustrates the study design and flow of participants and Table 1 summarises the schedule of enrolment and follow‐up assessment for trial participants.

**Figure 2 add15287-fig-0002:**
[figure not shown]
Flowchart of procedure

**Table 1 add15287-tbl-0001:** Schedule of enrolment and follow‐up assessments

Assessment	Time‐point			
	Baseline	1 month	3 months	6 months
Informed consent	x			
Eligibility screening	x			
Randomisation	x			
Intervention/comparator initiation	x			
Sociodemographic characteristics^a^	x			
Weekly alcohol consumption	x	x	x	x
AUDIT score and proportion of hazardous drinkers	x			x
Alcohol‐related problems or consequences and alcohol‐related injury				x
Use of healthcare services				x
Health‐related quality of life				x
Psychological measures	x			x
Engagement	x	x	x	x
Acceptability				x
Adverse events		x	x	x
Debriefing				x

^a^

Sociodemographic characteristics include: age, sex, ethnicity, education, occupation, income.

#### Eligibility assessment

Participants will self‐enrol into the study and potential participants will be asked to respond to a web‐based screening questionnaire to assess the inclusion and exclusion criteria, including the full AUDIT with the timeframe of the past 6 months (see Measures).

#### Consenting

If people meet the eligibility criteria they will be shown the information sheet (https://www.ucl.ac.uk/epidemiology‐health‐care/sites/epidemiology‐health‐care/files/participant_information_sheet.pdf) and informed that they will be re‐contacted on three occasions (at 1, 3 and 6 months). Participants will then be asked to provide consent online to participate in the study.

#### Baseline assessment

Participants will complete a web‐based assessment of sociodemographic measures (see Measures) and their contact details (email address, telephone number and postal address) for follow‐up assessments.

#### Randomisation

Participants who complete the baseline assessment will be randomised individually to intervention and comparator groups using block randomisation (block size of 50) and a random allocation sequence generated by an online automated algorithm (at a ratio of 1:1). Participants will be blinded to study arm. There will be no involvement of the researchers in the randomisation process, and there will be complete allocation concealment.

#### Intervention and comparator delivery

Participants will be emailed within 24 hours of the baseline assessment and randomisation with the recommendation to either use Drink Less (the intervention) or the NHS alcohol advice webpage (comparator). Participants allocated to the intervention condition will be provided with instructions on how to download the Drink Less app. Participants in both conditions will be provided with the contact details of the project team who will provide ongoing technical support, if required, during office hours. These emails will be co‐developed with public representatives.

#### Follow‐up assessments

Follow‐up assessments will be conducted 1, 3 and 6 months after baseline. The 6‐month follow‐up assessment will assess the primary and secondary outcome measures and psychological measures; the follow‐up assessments at 1 and 3 months will assess the self‐reported weekly alcohol consumption only. Participants will have up to 30 days to complete each survey to maximise data retention. Participants will be sent up to three automated emails with a link to a web‐based survey for the follow‐up assessments on days 0, 5 and 9. Participants who do not complete the web‐based follow‐up assessment will be sequentially offered opportunities to do so via phone (called once per day on days 10–17), mailed survey (on day 18) and by postcard (on day 30). Participants will be compensated with gift vouchers of up to £36 for completing the three surveys: £6 for the survey at 1 and 3 months; £12 at 6 months with an additional £12 if the 6‐month survey is completed within 24 hours.

At the 6‐month follow‐up, participants will indicate whether they are happy to be called for a short interview about their experience of the trial; there is no additional compensation for this telephone interview. Acceptability will then be measured after the 6‐month follow‐up via telephone interviews.

Participants will be asked whether they experienced any unexpected consequences, adverse events or other harms from participating in the study (in an open‐ended question at the 1‐, 3‐ and 6‐month follow‐up) and whether they have used any other forms of support for alcohol reduction (at the 6‐month follow‐up).

#### Debriefing

On completion of the trial, after the final follow‐up at 6 months, the comparator group will also be informed about the intervention, Drink Less.

### MEASURES

#### Sociodemographic measures

Sociodemographic measures will be assessed at baseline: age (in years, continuous), sex (% female), ethnicity (% white), education (% post‐16 educational qualifications), occupation (to derive social grade AB, C1, C2, D, E dichotomised into: ABC1 [managerial, professional and intermediate occupations] vs. C2DE [skilled, semi‐skilled, unskilled manual and lowest‐grade worked or unemployed]) and annual household income (% >£26 000 [29]).

### COVID‐19 measures

The recent COVID‐19 pandemic is affecting many aspects of people's lives in the UK. A lockdown is currently in place, limiting many people's ability to leave their homes, apart from essential journeys. Early evidence suggests that COVID‐19 may affect alcohol consumption, some lighter drinkers are drinking less than usual and some heavier drinkers are drinking more [30, 31, 32, 33]. To assess for the effects of the pandemic in the analysis, participants will respond to a brief COVID‐19 survey at each time point. Users will be asked ‘Do you currently feel like COVID‐19 is affecting your alcohol consumption and how you feel about drinking alcohol?’ If participants respond ‘no’ they will continue with the rest of the survey. Participants responding ‘yes’ will be asked to answer five follow‐up questions assessing the extent to which the pandemic is affecting their concerns about their alcohol consumption, their motivation to cut down and their patterns of consumption. Change in concerns about drinking will be measured by the question ‘Is COVID‐19 and its associated effects (e.g. financial, social or health) currently affecting how worried you feel about your alcohol consumption?’ followed by three response options: ‘more worried’, ‘no change’ and ‘less worried’. Change in motivation to reduce alcohol consumption will be measured by the question ‘Is COVID‐19 and its associated effects currently affecting your motivation to reduce your alcohol consumption?’ with three response options: ‘more motivated’, ‘no change’ and ‘less motivated’. Three questions measure changes in drinking patterns. Change in the frequency of drinking is measured by the question ‘Is COVID‐19 and its associated effects affecting how frequently you consume alcohol?’ with three response options: ‘consume alcohol more frequently’, ‘no change’ and ‘consume alcohol less frequently’. Change in the volume of alcohol consumed is measured by the question ‘Is COVID‐19 and its associated effects currently affecting how many units of alcohol you generally consume when you do drink?’ with three response options: ‘generally drink more units’, ‘no change’ and ‘generally drink less units’. Finally, change in the frequency of binge drinking is measured by the question ‘Is COVID‐19 and its associated effects currently affecting how often you consume 6 or more units of alcohol on a single occasion?’ with three response options: ‘more likely to consume 6 or more units on a single occasion’, ‘no change’ and ‘less likely to consume 6 or more units on a single occasion’. The date of national responses to COVID‐19 (e.g. lockdown) will also be monitored and recorded by the research team.

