Confidence intervals, effect sizes (partial η^2^ for ANOVA analyses, odds ratios for χ^2^ and regression analyses) and exact *P* values will be reported. Bayes factors will be calculated using a half normal distribution to specify the predicted effect (of a 2 UK unit reduction per week) with a peak at 0 (no effect) and the SD equal to the expected effect size with Robustness Regions reported to specify the range of expected effect sizes that support the same conclusion [60].

Finally, interactions will be assessed between group allocation with age, sex, ethnicity, education, occupation, income and COVID‐19 measures (survey and national responses) for primary and secondary outcomes. Where significant interactions are found the findings will be stratified, drawing on the PROGRESS‐Plus framework to explicitly consider health equity between the intervention and comparator group [61].

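### The COVID-19 gate question joins consumption and feelings with 'and', so participants affected in only one respect may skip all five follow-up items

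*Protocol article*

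**What the plan says.** The section on COVID-19 measures introduces a short survey, given at every time point, so that pandemic effects can be assessed in the analysis. The stated reason is that "COVID‐19 may affect alcohol consumption, some lighter drinkers are drinking less than usual and some heavier drinkers are drinking more".

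Entry to the survey is a single yes/no question: whether the participant currently feels that COVID-19 "is affecting your alcohol consumption and how you feel about drinking alcohol". The routing is explicit:

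- After 'no': "If participants respond ‘no’ they will continue with the rest of the survey".
- After 'yes': "Participants responding ‘yes’ will be asked to answer five follow‐up questions assessing the extent to which the pandemic is affecting their concerns", and also their motivation and drinking patterns.

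Behind the gate the two subjects are kept apart. Two items concern feelings. The first, on worry, is "followed by three response options: ‘more worried’, ‘no change’ and ‘less worried"; the second, on motivation, has the same three-way form. For consumption, "Three questions measure changes in drinking patterns": frequency, volume, and occasions of 6 or more units. Each of these also offers 'no change'.

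The answers have three later uses. The Analysis section compares them between arms at baseline. The section on analysis of primary and secondary outcomes tests interactions of allocation with several characteristics and with COVID-19 "measures (survey and national responses) for primary and secondary outcomes", and stratifies findings where an interaction is significant. The Process evaluation section models engagement and psychological measures by them.

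**The concern.** The gate is double-barrelled: it asks about two states at once and accepts one answer. Someone who drinks more, or less, because of the pandemic but feels no differently about drinking has no clearly correct reply. So has someone who is more worried but drinks as before. Taken at its word, the question calls for 'no' from both, and both then miss the item written for their case.

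This works against the survey's own design. Separate items, each with a 'no change' option, make sense only if one aspect can change without the other. The reason given for the survey is a change in consumption alone.

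At stake is the classification of individuals by pandemic effect. If affected people are filed with the unaffected, any difference in treatment effect between the two groups is diluted, and so are associations with engagement and psychological measures. Because the gate is put at each time point, the problem recurs.

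**Working it through.** The documents give no figure on this point, so there is none to reproduce. The check has two parts: the logic of the wording, and an illustration on assumed rates.

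**Wording and routing**

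| Aspects affected | Literal answer | Loose answer ('and' read as 'or') | Consequence of the literal answer |
|---|---|---|---|
| Both | yes | yes | All five items asked |
| Consumption only | no | yes | Three consumption items missed |
| Feelings only | no | yes | Two feelings items missed |
| Neither | no | no | None |

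The two readings differ only in the middle rows, and there the literal reading moves people only towards 'unaffected'. Nothing in the article tells participants to answer 'yes' if just one part applies.

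**Illustration of size**

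Assumptions, none from the documents: 40% of participants have consumption affected; a quarter of these have unchanged feelings; nobody has feelings alone affected; the treatment effect is the same in all affected people; the analysis contrasts gate 'yes' with gate 'no'. Let *q* be the share of consumption-only participants who read 'and' literally. The sample size of 5562 is from the Sample size section.

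- Consumption only: 40% × 25% = 10% of participants.
- Misrouted: *m* = 10% × *q*.
- Recorded 'no': 60% + *m*.
- Affected people within recorded 'no': *f* = *m* / (60% + *m*).
- The observed contrast is the true contrast × (1 − *f*), because the 'no' group's effect is a mixture with weight *f* on the affected.

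| *q* | Misrouted | Of 5562 | Recorded 'no' | *f* (dilution) | Contrast multiplied by |
|---|---|---|---|---|---|
| 0 | 0% | 0 | 60% | 0% | 1.00 |
| 0.5 | 5% | 278 | 65% | 5/65 = 7.7% | 0.92 |
| 1 | 10% | 556 | 70% | 10/70 = 14.3% | 0.86 |

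**Sensitivity to the assumed rates**

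The illustration leaves out people with feelings alone affected. Suppose instead that each aspect is affected in 30%, with 70% overlap.

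- Both: 0.7 × 30% = 21%.
- Either: 30% + 30% − 21% = 39%.
- Exactly one: 39% − 21% = 18%.
- Recorded 'yes': 21% + (1 − *q*) × 18%, which is 39%, 30% and 21% at *q* = 0, 0.5 and 1.
- Share of affected people missed: 0%, 9/39 = 23% and 18/39 = 46%.

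The upper end thus depends heavily on the assumed rates. The lower end is zero in every case.

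**What is outside the reach of the gate**

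- The primary model adjusts for baseline consumption only; the COVID-19 answers are not in it.
- Weekly consumption is scheduled at baseline, 1, 3 and 6 months (Table 1), whatever the gate answer.
- Dates of national responses are recorded by the research team and do not pass through the gate.

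**The case against.** The strongest reply is that respondents need not parse a screener strictly. Many may answer 'yes' if either part applies, and the survey accommodates this, since the follow-up items each allow 'no change'. That stands as far as it goes: the literal reading is available but not compelled, and the loss may be nil. It does not remove the defect. The wording leaves the reading to each participant, and someone answering the gate for the first time has not seen the items that would show a one-sided 'yes' is welcome.

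Three further objections stand:

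- The illustrative rates are invented, and the article does not fix how the survey answers enter the interaction models. The 14% is therefore the top of one assumed range and not an estimate.
- Those who answer 'yes' still report consumption and feelings separately. The distinction is lost only for people with one aspect affected who answer 'no'.
- A gate serves brevity, and the protocol treats low response burden as important when it justifies its primary outcome measure. This argues for keeping a gate, though not for this wording.

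A reader might also infer that the trial will understate pandemic-related increases in drinking, or that the baseline comparison of arms is biased. The documents support neither. Increases and decreases pass through the same gate, and consumption itself is measured regardless; only its attribution to the pandemic is lost. Baseline answers precede allocation, so misrouting there has no reason to differ by arm.

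**Conclusion.** The point holds as a minor flaw in item wording. The gate can be read as requiring both aspects to be affected, and on that reading participants with one aspect affected are recorded as unaffected. The expected direction is under-recording of self-attributed pandemic effects, whether drinking rose or fell. The consequence is dilution of the COVID-19 survey interactions and of the process modelling by those measures.

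The size cannot be determined from the documents. On the 40% and one-quarter assumptions, misrouting is 0% to 10% of participants and dilution 0% to about 14%, according to how many read 'and' literally; other assumed rates give other upper limits. The dates of national responses offer a second pandemic measure in the same analyses, but they cannot recover an individual's missing answers.

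It would be tempting to conclude that the trial's main result is compromised. It is not: the primary estimate does not use these answers.

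**What to change.** In the gate question, replace the 'and' between consumption and feelings with 'and/or'. Keep the gate, so that people affected in neither respect still skip the five items. Showing the items to everyone would also close the gap, but it adds five questions at four time points for those who would have answered 'no', against the protocol's aim of limiting burden.

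If data collection has begun, report the gate wording used. In the analysis, code the five items of 'no' responders as not asked rather than as 'no change'.

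The cost is a one-word edit to an online survey, with slightly more participants answering five short items. A change made mid-trial also reduces comparability between answers under the two wordings, so the date of the change should be recorded.
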